First, with respect to children’s distinctions between religious and moral norms, we hypothesize that children will (1a) deem moral violations less permissible and more severely negative than religious violations, (1b) provide religious justifications more often when explaining judgments about religious norm violations and refer to victim welfare more often when explaining judgments about moral violations, (1c) be more likely to judge that religious norms are alterable by religious authorities than to judge that moral norms are alterable by religious authorities, and (1d) be more likely to apply moral norms to characters who are not members of the target religion than to apply religious norms to members of the target religion. (For previous work that has informed these hypotheses, see [70, 72–78].)

Second, with respect to children’s distinctions between religious and conventional norms, we predict that children will (2a) provide religious justifications more often when explaining judgments about religious norm violations and refer to secular authorities (e.g., teachers, parents) more often when explaining judgments about conventional violations, and (2b) be more likely to apply conventional norms to characters who are not members of the target religion than to apply religious norms to members of the target religion. (See [70, 72–78].)

To test these hypotheses, we will examine the main effects of norm type (religious vs. moral, religious vs. conventional) on children’s initial permissibility and severity ratings (relevant to hypothesis 1a); their open-ended justifications of their permissibility ratings (relevant to hypotheses 1b and 2a); their permissibility and severity ratings in the “alterability” portion of the block (relevant to hypothesis 1c); and their final permissibility and severity ratings for characters who are not members of the target religion (relevant to hypotheses 1d and 2b). For predictions about alterability and scope (hypotheses 1c, 1d, and 2b), we will also examine the main effect of norm type on the *differences* between children’s initial and later responses, i.e., compare children’s permissibility and severity ratings for characters who are not members of the target religion to their own initial permissibility and severity ratings for members of the target religion.

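### Norm Violations task: hypotheses 1d and 2b cross norm type with membership and do not match their listed test, and the plan does not say whether later ratings or within-child change decides 1c, 1d and 2b

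*Protocol article*

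**What the plan says.** All of this stands in the protocol article, Norm Violations task.

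- **Definitions (Task design and procedure).** After the initial permissibility and severity ratings, alterability is measured by having the child rate the same violation again, supposing that a religious authority allows it. Scope is whether the norm reaches beyond the target group, measured by having the child rate the same violation again when a non-member commits it.
- **1a (Planned analyses).** Children will "deem moral violations less permissible and more severely negative than religious violations".
- **1c.** Children will "be more likely to judge that religious norms are alterable by religious authorities than to judge that moral norms are alterable by religious authorities".
- **1d.** Children will "be more likely to apply moral norms to characters who are not members of the target religion than to apply religious norms to members" (meaning people inside the target group).
- **2b.** Children will "be more likely to apply conventional norms to characters who are not members of the target religion than to apply religious norms to members" (again meaning people inside the target group).
- **Tests listed first.** The main effect of norm type is examined for 1c on ratings in the alterability "portion of the block (relevant to hypothesis 1c"), and for 1d and 2b on "their final permissibility and severity ratings for characters who are not members of the target religion (relevant to hypotheses 1d and 2b").
- **Tests added.** "For predictions about alterability and scope (hypotheses 1c, 1d, and 2b), we will also examine the main effect of norm type on the" (the outcome is each child's change from first to later answer). The explanatory clause describes comparing ratings for non-members "to their own initial permissibility and severity ratings for members of the target religion".

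The plan does not say which of the two analyses decides a hypothesis, or what follows if they disagree.

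**The concern.** There are two separate problems.

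**Wording.** As worded, 1d and 2b set a moral or conventional norm with a non-member against a religious norm with a member. Neither uses the rating of a non-member who breaks a religious norm, which is the only rating that shows whether religious norms are confined to the group. The hypothesis and its listed test are therefore different contrasts.

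**Baseline.** Alterability and scope are both defined by asking again about the same violation, so they are changes from the child's first answer. A test on later ratings alone mixes that change with where the child started. Since 1a expects religious violations to start out more permissible than moral ones, 1c and 1d can look confirmed when no child changes an answer. For 2b the plan predicts no baseline direction between religious and conventional norms, so the bias could go either way.

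The same section says that the age and sample comparisons of central interest will probably extend these analyses. Religious norms differ by sample (Table 5), so baseline permissibility may differ by sample too.

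**Working it through.** The protocol gives no expected rate, alpha or effect size for this task, so there is no figure to reproduce. All rates, the correlations and the 5% level below are assumptions. The 75 children are the planned US minimum per sample (Sample size, US samples). Each child rates two religious norms, one moral and one conventional.

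**1. Identity.** Let *o* be the proportion judging the moral or conventional violation *not okay* and *r* the same for the religious violation, with 0 = initial and 1 = later (authority permits it, or non-member actor).

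- Later-rating gap: o1 − r1 = (o0 − r0) + [(o1 − o0) − (r1 − r0)], that is, baseline gap plus change contrast.
- Literal 1d/2b gap: o1 − r0. It does not contain r1.

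**2. Wording against listed test.** Assume conventional 40% for anyone, and religious 70% for members and 30% for non-members.

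- 2b as worded: 40 − 70 = −30 points.
- Listed test: 40 − 30 = +10 points.
- Change contrast: (40 − 40) − (30 − 70) = +40 points.

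The sentence disagrees in sign with both planned analyses, and the two analyses agree with each other.

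**3. 1c with no change at all.** Take *okay* rates p1 (religious) and p2 = 0.02 (moral), one norm of each type, and answers independent within child. With d = p1 − p2, z = d / sqrt((p1(1 − p2) + p2(1 − p1) − d²) / 75).

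- p1 = 0.10: 0.08 / sqrt((0.116 − 0.0064) / 75) = 2.09
- p1 = 0.20: 0.18 / sqrt((0.212 − 0.0324) / 75) = 3.68
- p1 = 0.40: 0.38 / sqrt((0.404 − 0.1444) / 75) = 6.46

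The change contrast is exactly 0 in all three.

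**4. Paired simulation.** 75 children, 4000 runs, two religious norms averaged, shared child and norm effects, two-sided 5% t test. Cells give the gap and the share of runs significant.

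| Assumed *not okay* rates, initial → later | Later ratings | Literal 1d/2b | Change |
|---|---|---|---|
| Equal change: moral .95→.85, religious .60→.50 | +.35; 100% | +.25; 99.6% | 0; about 5% |
| 2b true: conventional .40→.38, religious .80→.50 | −.12; 48%, wrong direction | −.42; 100%, wrong direction | +.28; 99% |
| 1d false: moral .98→.88, religious .60→.60 | +.28; over 99% | +.28; over 99% | −.10; 48%, against 1d |
| Equal baselines, 1d true: moral .90→.90, religious .90→.50 | +.40; 100% | 0; about 5% | +.40; 100% |

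**5. Range.** Hold an equal drop of .10, with the moral norm at .85 for non-members. Religious baselines of .50, .60, .70, .80, .90 and .95 give spurious later-rating gaps of .45, .35, .25, .15, .05 and 0. A two-proportion calculation with 75 per group, treated as independent, finds the first five significant about 100%, 99.8%, 94%, 60% and 12% of the time. At .95 the baselines are equal and there is no gap.

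**The case against.** The strongest reply is that the remedy is already in the plan: the analysis of initial-to-later differences is named for exactly 1c, 1d and 2b. In the simulation it had the right direction wherever a true difference existed, and about 5% false positives under equal change. Which of two stated analyses takes precedence is also a detail that an article may leave to a fuller analysis plan. This largely stands and limits the finding. What survives is that the article names the later-rating test as a test of each hypothesis in its own right, and that its explanatory clause covers scope but not alterability.

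Three stronger readings are tempting, and the document does not support them.

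- *The plan as a whole will reach wrong or reversed conclusions.* In steps 2 and 3 the planned change contrast gives the right answer. The −30 points belongs to a sentence that no listed analysis tests. A wrong conclusion follows only if the later-rating result is allowed to decide.
- *A child who first says okay cannot move, so difference scores fail.* The child also rates severity on each occasion, and an initial *okay* can become *not okay*. Floor and ceiling effects are real but partial.
- *Only pairs first judged not okay should be analysed.* That selects on a noisy baseline. If repeat answers were independent draws with 40% *okay* for religious and 2% for moral violations, and nothing truly changed, switch rates would be 40% v 2%. That would falsely confirm 1c, while the mean change is 0 for both.

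**Conclusion.** The point holds as a minor correction. The wording fault in 1d and 2b is certain from the text: both contradict the task's own definition of scope and the test listed for them. The crossed comparison is a fault of the hypotheses, not of the listed test, which compares non-members with non-members.

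The baseline problem is certain in form and conditional in size. It runs from nil when initial ratings are equal to near-certain false confirmation when they are far apart. For 1c and 1d the bias is towards confirmation if 1a is right; for 2b it can go either way. These sizes rest on assumed rates and on 75 children.

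The consequence is limited. The article calls the protocol largely exploratory (Manuscript overview; Discussion), the change analysis is already planned, and every rating needed is already collected.

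**What to change.** 1. Change the second comparator in 1d and 2b from members to non-members, so that both sides concern characters outside the target religion. State each as a norm type by membership contrast: moving from member to non-member lowers application of the norm less for moral (1d) or conventional (2b) norms than for religious ones.
2. Name the planned within-child contrast, norm type by initial v later rating, as the deciding test for 1c, 1d and 2b. One form is the interaction in a repeated-measures model that uses all child-norm pairs, with its scale stated.
3. Spell the contrast out for 1c as the rating after the authority's permission against the initial rating.
4. Report later-rating levels by norm type as description.
5. Use an analysis restricted to pairs first judged *not okay* only as a sensitivity analysis, if at all.

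The cost is wording and model specification, with no new data. The downside is that change scores are somewhat noisier than levels and remain subject to floor and ceiling effects.

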At the beginning of each block, the child is presented with a grayscale silhouette of character. The researcher introduces the character as an adult member of the target religious group who habitually violates a religious, moral, or conventional norm; see Table 5 for norms selected for each US sample. There is no visual depiction of the specific norm violation, and silhouettes are matched with stories at random. The child is then asked a series of questions about the norm in question, in a fixed order. First, the child is asked about the *permissibility* of the norm violation (“Is that okay or not okay?”) and is asked to explain their response (“Why is that [okay/not okay]?”). Second, the child is asked to rate the *severity* of the norm violation (“And how good/bad is it that…?”) on a three-point scale (“not good/bad,” “just a little bit good/bad,” or “very good/bad”). Third, the child is asked about the *alterability* of the norm by religious authorities; this is gauged by asking the child to reassess the permissibility and severity of the norm violation if a religious authority declared the norm violation to be okay (“What if [God/another religious authority] said that it was okay to…–then would it be okay for…? And how good/bad would that be?”). Fourth, the child is asked about the *scope* of the norm, i.e., whether it applies beyond the target religious group; this is gauged by asking the child to reassess the permissibility and severity of the norm violation if it were committed by a non-group member (“This is a man named Morgan. Morgan is not Muslim. Morgan …”). The child answers all of these questions for a single norm before proceeding to the next block, which features a different norm.

**Table 5 pone.0292755.t005:** Sample-specific item selection for the Norm Violations task (including the familiarity assessment at the end of the task), for the five religions included in US samples.

	Religion				
	*Protestantism*	*Catholicism*	*Church of Jesus Christ of L*.*D*.*S*.	*Judaism*	*Islam*

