** *Religious Norm Violation #1* **					
*Item*	This is a [woman/man] named [character]. [Character] is Christian. [Character] never goes to church. [She/He] could, but [she/he] chooses not to.	This is a [woman/man] named [character]. [Character] is Catholic. [Character] never goes to church. [She/He] could, but [she/he] chooses not to.	This is a [woman/man] named [character]. [Character] is a member of the Church of Jesus Christ. [Character] never gives money to the church.	This is a [woman/man] named [character]. [Character] is Jewish. [Character] never lights candles on Friday nights.	This is a [woman/man] named [character]. [Character] is Muslim. [Character] never does [her/his] five daily prayers.
*Character*, *ingroup*	Christina/Mark	Christina/Mark	Christina/Mark	Rebecca/David	Yara/Danny
*Character*, *non-ingroup*	Jesse	Jesse	Jesse	Jesse	Jesse

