** *Religious Norm Violation #2* **					
*Item*	This is a [woman/man] named [character]. [Character] is Christian. [Character] was never baptized—so a priest or pastor never put water on [her/his] head.	This is a [woman/man] named [character]. [Character] is Catholic. [Character] was never baptized—so a priest or pastor never put water on [her/his] head.	This is a [woman/man] named [character]. [Character] is a member of the Church of Jesus Christ. [Character] drinks coffee.	This is a [woman/man] named [character]. [Character] is Jewish. [Character] eats foods that are not kosher.	This is a [woman/man] named [character]. [Character] is Muslim. [Character] eats foods that are not halal.
*Character*, *ingroup*	Natalie/Luke	Natalie/Luke	Natalie/Luke	Rachel/Adam	Yasmina/Rami
*Character*, *non-ingroup*	Morgan	Morgan	Morgan	Morgan	Morgan

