** *Moral Norm Violation* **					
*Item*	This is a [woman/man] named [character]. [Character] is Christian. [Character] hits other people for no reason.	This is a [woman/man] named [character]. [Character] is Catholic. [Character] hits other people for no reason.	This is a [woman/man] named [character]. [Character] is a member of the Church of Jesus Christ. [Character] hits other people for no reason.	This is a [woman/man] named [character]. [Character] is Jewish. [Character] hits other people for no reason.	This is a [woman/man] named [character]. [Character] is Muslim. [Character] hits other people for no reason.
*Character*, *ingroup*	Mary/Chris	Mary/Chris	Mary/Chris	Leah/Michael	Mona/Kareem
*Character*, *non-ingroup*	Jordan	Jordan	Jordan	Jordan	Jordan

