** *Conventional Norm Violation* **					
*Item*	This is a [woman/man] named [character]. [Character] is Christian. [Character] wears socks on [his/her] hands.	This is a [woman/man] named [character]. [Character] is Catholic. [Character] wears socks on [his/her] hands.	This is a [woman/man] named [character]. [Character] is a member of the Church of Jesus Christ. [Character] wears socks on [his/her] hands.	This is a [woman/man] named [character]. [Character] is Jewish. [Character] wears socks on [his/her] hands.	This is a [woman/man] named [character]. [Character] is Muslim. [Character] wears socks on [his/her] hands.
*Character*, *ingroup*	Grace/Matthew	Grace/Matthew	Grace/Matthew	Sarah/Samuel	Leila/Nidal
*Character*, *non-ingroup*	Riley	Riley	Riley	Riley	Riley

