** *Familiarity assessment* **					
*Reference religious group*	Christians	Catholics	members of the Church of Jesus Christ	Jews	Muslims
*Norm #1*	going to church	going to church	giving money to church	eating food that is kosher	eating food that is halal
*Norm #2*	getting baptized	getting baptized	not drinking coffee	lighting candles on Friday night	praying five daily prayers

Unaffiliated children in the US are shown the version of the protocol that corresponds to the religion with which they are likely most familiar (see main text for details). See main text for descriptions of network-wide guidelines for item selection. “L.D.S.” stands for “Latter-day Saints.”

^a^ If the researcher becomes aware that the child is more familiar with the term “Hashem” or “Adonai” then the more familiar term is used in place of “God” throughout the Child Protocol.

After completing all four blocks of questions, the child is asked a series of questions intended to gauge awareness of religious norms in general and familiarity with the two religious norms featured in this task. First, the researcher asks the child, “Are there any rules that [target religious group members] should follow? Like anything they are supposed to do, or not supposed to do?” If the child does not provide a meaningful response, the researcher follows up with, “What are things that only people who go to the same [house of worship] as you do, or do not do?” Then, the researcher asks the child directly about each of the two religious norms featured in this task, by asking, “What about [target religious group members] [following the religious norm]?–is that something you have heard of?” If the child has already mentioned one or both of the religious norms in the initial open-ended question, the researcher skips the corresponding follow-up question(s).

Across the four blocks, we include two religious norms, one moral norm, and one conventional norm.

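### In the US Norm Violations task, the norm-type effect for hypothesis 1a mixes norm type with act versus omission: fully in the Protestant and Catholic versions, by half in the other three

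*Protocol article*

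**What the plan says.** In the Norm Violations task each child judges four characters, and across the blocks "we include two religious norms, one moral norm, and one conventional norm". The task description presents each character as "an adult member of the target religious group who habitually violates a religious, moral, or conventional norm".

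Table 5 fixes the US items. The moral item is that the character "hits other people for no reason" and the conventional item is that the character "wears socks on [his/her] hands"; both are the same in all five versions. The religious items differ by version. The church-attendance item adds "She/He] could, but [she/he] chooses not to". The baptism item explains itself with "so a priest or pastor never put water on [her/his] head".

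Hypothesis 1a is that children will "deem moral violations less permissible and more severely negative than religious violations". Under Planned analyses, "we will examine the main effects of norm type (religious vs. moral, religious vs. conventional" covers initial permissibility and severity, justifications, and the later alterability and scope ratings. For 1c, 1d and 2b the plan adds differences between a child's initial and later ratings. Differences by age and sample are called of central interest but exploratory, and item-level analyses are also planned.

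The network-wide guidelines for this task state openly that religious norms may be prescriptive or proscriptive across samples. The planned contrasts do not use that distinction.

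**The concern.** A norm-type main effect can be read as norm type only if the items being compared do not also differ systematically in some other way that moves the ratings. Here they do. The moral and conventional characters do something; most of the religious characters fail to do something. If children judge failing to act more leniently than acting, 1a gains support even if they make no distinction between religious and moral norms.

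The imbalance also differs between versions, so part of any norm type by sample difference could come from item form. The baptism item stands further apart: it describes a single event that did not happen rather than a habit, and it says nothing about whether the character chose this.

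**Working it through.** The article gives no power, alpha or effect size for this task, so there is no stated figure to reproduce. The check is a count from Table 5 followed by simple algebra.

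**Step 1: classify the items.** An act is something the character does; an omission is something never done, or never undergone.

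| Version | Religious #1 | Religious #2 | Moral | Conventional | Religious omissions |
|---|---|---|---|---|---|
| Protestant | church attendance: omission | baptism: omission | act | act | 2 of 2 |
| Catholic | church attendance: omission | baptism: omission | act | act | 2 of 2 |
| Latter-day Saints | giving money: omission | coffee: act | act | act | 1 of 2 |
| Jewish | Friday candles: omission | non-kosher food: act | act | act | 1 of 2 |
| Muslim | daily prayers: omission | non-halal food: act | act | act | 1 of 2 |

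Total religious omissions: 2 + 2 + 1 + 1 + 1 = 7 of 10. Moral and conventional omissions: none.

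**Step 2: bias in the contrast.** Let b be the shift in a rating due to omission rather than act. With no true norm-type effect, the religious-minus-moral contrast equals b × (share of religious items that are omissions):

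- Protestant, Catholic: b × 2/2 = 1.0b
- Latter-day Saints, Jewish, Muslim: b × 1/2 = 0.5b
- Equal average over the five versions: b × 7/10 = 0.7b
- Difference between the two sets of versions: 1.0b − 0.5b = 0.5b

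The religious-minus-conventional contrast behaves in the same way.

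**Step 3: illustrative size.** The documents do not give b. Suppose omissions are judged not okay 20 percentage points less often than acts (assumption; range 10 to 30). The artefact is then 20 points (10 to 30) in the Protestant and Catholic versions, 10 points (5 to 15) in the other three, and 10 points (5 to 15) between the two sets.

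On a standardised scale, with b in SDs of the within-child difference, n = 75 (the planned US minimum per sample) and an assumed two-sided alpha of 0.05, the chance of a significant norm-type effect from b alone is about Φ(b × share × √75 − 1.96):

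| Assumed b | Share 1.0 | Share 0.5 |
|---|---|---|
| 0.2 | 41% | 14% |
| 0.3 | 74% | 25% |
| 0.5 | 99% | 58% |

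**Step 4: which tests are exposed.** For a given item, the initial rating contains b × (1 if omission, 0 if act). If the alterability or scope rating of that item contains the same amount, the within-item difference removes it. The difference-score tests of 1c, 1d and 2b are therefore protected against a constant shift, though not against one that changes between questions or is distorted by the ends of a short scale. Hypothesis 1a has no such difference, and the alterability and scope ratings taken on their own keep the full share.

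**Step 5: can analysis separate the two?** In the Latter-day Saints, Jewish and Muslim versions, one act-form religious item can be set against the act-form moral and conventional items. In the Protestant and Catholic versions there is no act-form religious item and no omission-form moral or conventional item, so no covariate or item-level analysis within those versions can separate item form from norm type.

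**The case against.** The article is not silent on variation between items. It states the prescriptive/proscriptive variation as a deliberate choice made for cultural fit, plans item-level analyses, and warns in the Discussion that comparisons across samples must allow for differences between protocol versions. It describes the protocol as largely exploratory. Items also differ in other ways, for example in whether there is a victim. All of this stands, and it lowers the weight of the point. It does not remove it: the general warning concerns comparisons between samples rather than the contrast within a sample, and item-level analysis cannot help in the two versions where every religious item is an omission.

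Three stronger readings are tempting and are not supported.

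- A reader might infer that every Norm Violations hypothesis is compromised. Hypotheses 1b and 2a concern the content of justifications, and nothing in the documents indicates how item form would produce it. The difference scores for 1c, 1d and 2b are largely protected.
- A reader might infer that 1a will be falsely supported, or that sample differences must appear. That needs a known b. If b is zero there is no bias, and if omissions are judged more harshly the test of 1a is conservative.
- A reader might want to move the main test onto the act-form religious items. These are one item each in three versions, all of them food or drink rules, whereas the guidelines want varied religious content. They also sit in the three samples for which the Sample size section reports serious recruitment difficulty, and a sample that stays below 75 enters only pooled analyses.

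**Conclusion.** The point holds for hypothesis 1a and for the undifferenced alterability and scope ratings. Norm type is fully confounded with item form in the Protestant and Catholic versions (2 of 2 religious items are omissions) and half confounded in the other three (1 of 2). The exploratory norm type by sample comparison inherits a difference of 0.5b.

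The counts come directly from Table 5. The size in points or in power rests entirely on an assumed b, and so does the direction; only if omissions are judged more leniently does the bias favour 1a. The counts cover the five US versions. The unaffiliated US sample receives a mixture of them, with the Protestant version as the fallback, so its share depends on that mixture.

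The weakness is that the analysis does not use a dimension the guidelines already name. The variation between items is itself disclosed.

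**What to change.** Keep the planned main effect and add the following to the Norm Violations planned analyses:

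1. Code each item as act or omission (equivalently here, proscriptive or prescriptive norm).
2. Report 1a separately by item form. Use the act-form Religious Norm #2 items in the Latter-day Saints, Jewish and Muslim versions as a like-for-like sensitivity contrast, noting that all three are food or drink rules.
3. Make sample comparisons on Religious Norm #1, which is an omission in all five versions. Note that only the church-attendance wording states choice, so these items match on form but not on stated choice.
4. Report the baptism item separately, because it is not habitual and choice is not stated.
5. State that in the Protestant and Catholic versions a religious-moral or religious-conventional difference in ratings cannot be attributed to norm type apart from item form.

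No item changes or new data are needed. The cost is a little more analysis and reporting, and a narrower conclusion for two versions.
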